### **8. Evaluation of Efficacy**

#### 8.1 Efficacy Endpoints

##### 8.1.1 Primary Endpoint

Proportion of patients in whom AF or non-sustained or sustained VT is detected

##### 8.1.2 Secondary Endpoints

1. Proportion of patients with pauses ≥4.5 s
2. Proportion of patients with bradycardia <30 bpm
3. Proportion of patients with high-grade AV block
4. Proportion of patients receiving pacemaker, ICD, ablation, or antiarrhythmic therapy
5. All-cause mortality
6. Cardiovascular mortality
7. Proportion with hospitalizations for CV disease/HF
8. Proportion who experienced stroke

#### 8.2 Evaluation and Recording of Efficacy Endpoints

The main analysis uses 1-year data; after all have reached 3 years, a final analysis is done.

#### 8.3 Method and Timing of Analysis for Efficacy Endpoints

See Section 10 for statistical methods.

**9. Evaluation of Safety**

**9.1 Safety Endpoints**

The following safety endpoints will be assessed:

1. **Incidence of adverse events (AEs) related to ILR implantation:**
   - This includes any complications arising from the device implantation procedure, such as infection, erosion, bleeding, or device migration.
   - AEs will be classified based on their severity and relationship to the investigational device.
2. **Incidence of device malfunctions:**
   - Malfunctions include battery failure, data transmission issues, signal loss, and other device-related failures.
   - Malfunctions that lead to clinical consequences (e.g., an inability to detect arrhythmias) will be documented separately.

An **adverse event (AE)** is defined as any undesirable experience occurring in a subject, whether related to the study intervention or not. **A serious adverse event (SAE)** includes events that result in hospitalization, life-threatening conditions, or significant disability.

**9.2 Evaluation, Recording, and Analysis of Safety Endpoints**

1. **Evaluation Period:** From the date of ILR implantation until three years post-implantation.
2. **Data Collection:**
   - All AEs and device malfunctions will be recorded in the case report form (CRF).
   - Events will be categorized based on severity, expectedness, and causality.
3. **Reporting:**
   - Serious AEs will be reported within 24 hours to the Certified Review Board (CRB) and regulatory authorities as required.
   - Routine AE reports will be submitted periodically.

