##### 7.1.2 ILR Implantation

- Within 30 days after registration, the ILR is implanted (usually outpatient basis, possibly inpatient if necessary). If it cannot be done within 30 days, protocol treatment is discontinued.
- Implantation steps (outline):
  1. Implant site: 4th intercostal space in the left anterior chest.
  2. Local disinfection with povidone-iodine, local anesthesia, small incision, creation of a subcutaneous pocket (~8 mm depth).
  3. Insert the ILR device using the supplied introducer.
  4. Confirm adequate ECG signal via the programmer (Reveal LINQ Mobile Manager) before closing.
  5. No prophylactic antibiotics are used.
  6. The device is programmed for continuous monitoring (remote monitoring) settings.

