##### 7.1.5 End of the Study

- At 3 years post-implantation, the subject completes the protocol observation period, and the ILR is explanted.
- If an adverse event or device malfunction (e.g., battery depletion) necessitates explantation, the study observation ends at that time.
- If a new device (e.g., a permanent pacemaker) is implanted, rendering ILR monitoring moot, ILR is explanted, and observation ends.
- If follow-up is no longer feasible, the ILR is explanted, and observation ends.
- Explantation is generally performed on an outpatient basis with local anesthesia. The removed ILR is discarded per institutional procedures.
- The MyCareLink Relay Home Communicator is discarded as non-burnable trash.

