**10. Statistical Analysis**

**10.1 Analysis Sets**

1. **Full Analysis Set (FAS):** Includes all enrolled subjects who received an ILR.
2. **Per Protocol Set (PPS):** Includes subjects who strictly adhered to the study protocol without major deviations.
3. **Safety Analysis Set (SAS):** Includes all subjects implanted with an ILR for safety evaluations.

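### The safety period closes at three years, when the ILR is removed, so complications after removal are not counted in the reported safety rate

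*Protocol*

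**What the plan says.** Protocol section 9.2 gives the safety evaluation period as "From the date of ILR implantation until three years post-implantation".

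Section 7.1.5 places removal at the end of that period: "At 3 years post-implantation, the subject completes the protocol observation period, and the ILR is explanted". Removal is a procedure: "Explantation is generally performed on an outpatient basis with local anesthesia". The same section covers earlier removals. Where an adverse event or malfunction "necessitates explantation, the study observation ends at that time". Observation likewise ends when another implanted device makes the ILR redundant, or when follow-up is no longer possible.

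Section 9.1 defines the first safety endpoint as adverse events related to ILR implantation and says that it includes "any complications arising from the device implantation procedure", with infection, erosion, bleeding and migration as examples. Explantation is not named. The schedule in section 7.2.1 has no explantation column and no assessment after removal.

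The safety analysis set in section 10.1 is worded: "Includes all subjects implanted with an ILR for safety evaluations".

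**The concern.** Each subject is planned to undergo two procedures under local anaesthesia because of the study: insertion and removal. The stated safety period covers the time after the first and stops when the second is due. A wound infection or bleed that appears in the days after a scheduled removal falls after the period has closed. After an early removal, section 7.1.5 has already ended observation, although the section 9.2 period would still be running.

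The complication rate is one of the study's two safety endpoints. Section 13.2 describes the burden as limited and severe physical risk as unlikely, and section 3 foresees a later trial aimed at wider indications. Leaving removal complications out of the numerator can only lower the reported rate. With 35 subjects, one event more or less visibly changes the result.

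**Working it through.** The plan states no figure to reproduce for this point. The check is a comparison of the sections, followed by an illustration of size.

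**Timeline, scheduled removal.** The end of the safety period is 3 years after implantation (9.2). Scheduled removal is 3 years after implantation (7.1.5). Time at risk after removal within the period: 3 years − 3 years = 0 days. An event on the day of removal is a boundary case.

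**Timeline, early removal.** Suppose a device comes out at month 18. Section 9.2 leaves 36 − 18 = 18 months of safety period. Section 7.1.5 leaves none. The two sections conflict.

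**Endpoint.** Section 9.1 ties the endpoint to implantation. A complication of removal has no clear place in it, even if it falls inside the period.

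**Inputs for the size.**
- Number of removals, n: up to 35 (planned enrolment, section 10.2). This is an upper bound, since some subjects may die or leave before removal.
- Complication rate of removal, p: not given anywhere. The only related figure is about 1.5% in section 3, an overall complication rate in ILR recipients and not a rate per procedure. I therefore assume half to double that figure: 0.75%, 1.5% and 3%.

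**Formulas.** Expected uncounted events = n × p. Chance of at least one = 1 − (1 − p)^n.

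| Assumed p | Expected events, n = 35 | Chance of at least one |
| --- | --- | --- |
| 0.75% | 35 × 0.0075 = 0.26 | 1 − 0.9925^35 = 23% |
| 1.5% | 35 × 0.015 = 0.53 | 1 − 0.985^35 = 41% |
| 3% | 35 × 0.03 = 1.05 | 1 − 0.97^35 = 66% |

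**Effect on the reported rate** (exact two-sided 95% limits, 35 subjects):
- 0 of 35: 0%, upper limit 10.0%
- 1 of 35: 2.9% (0.07% to 14.9%)
- 2 of 35: 5.7% (0.7% to 19.2%)

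One uncounted event therefore separates an estimate of 0% from one of 2.9%.

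**The case against.** The best case for the plan is that it records more than section 9.2 suggests. Section 5.6 continues follow-up of suspected study-related events beyond the participation period until they resolve. Section 7.6 requires clinical follow-up after discontinuation. Section 11 lists the course after discontinuation among the data held in the CRF. Section 9.2 sends all adverse events to the CRF, and sections 9.3 and 10.5 summarise adverse events without restricting them to implantation. The endpoint text in 9.1 is introduced as inclusive, and erosion and migration are complications of carrying a device rather than of inserting it.

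Much of this stands. A reader might infer that nothing is captured after removal. The documents do not support that: patients are followed, events may well be recorded, and for early removals the calendar period in 9.2 is still open. What does not follow is that these events are counted. None of these provisions extends the evaluation period or brings removal into the endpoint.

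Two further inferences also go too far.
- **Attempted implants.** A reader might take the analysis-set wording to exclude a patient whose signal check fails. In section 7.1.2 the check ("Confirm adequate ECG signal via the programmer (Reveal LINQ Mobile Manager) before closing") comes after the device has been inserted, and section 10.3 excludes only those who withdraw before implantation. No rule excludes attempted implants; the wording is merely loose.
- **Deaths.** A reader might infer that deaths are lost because the serious adverse event definition lists "events that result in hospitalization, life-threatening conditions, or significant disability". That list is also introduced as inclusive, deaths are recorded under section 7.2.2, and mortality is a secondary endpoint.

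Finally, the expected effect is at most about one event in an exploratory single-arm study.

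**Conclusion.** The point holds for counting and reporting, not for patient care. As written, complications that arise after a study-mandated removal are left out of the reported safety rate, and sections 7.1.5 and 9.2 disagree about early removals.

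The size is about 0.3 to 1 uncounted event, with a 23% to 66% chance of at least one. This rests on an assumed rate of 0.75% to 3% and on up to 35 removals; the protocol supplies no rate for removal. The omission can only make the rate look better, but nothing in the protocol suggests that this was intended.

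The primary analysis of arrhythmia detection uses 1-year data (sections 5.1 and 8.2) and is unaffected.

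**What to change.** - **Section 9.1:** state that the first safety endpoint covers adverse events related to ILR implantation, presence or explantation.
- **Section 9.2:** extend the safety period past explantation, scheduled or early, by a fixed interval. The investigators should set its length; the protocol gives no basis for a particular figure.
- **Sections 5.6, 7.1.5 and 9.2:** reconcile them so that the end of observation, the follow-up of study-related events and the safety period agree, and events after removal are counted.
- **Section 10.1 (minor clarification):** word the safety analysis set as all subjects in whom the implantation procedure was started.

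The cost is protocol wording and one CRF field. Outpatient visits every 1 to 3 months are part of usual care (section 7.1.4) and could supply the data where they continue after removal. The reported complication rate may be slightly less favourable.

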**9.3 Statistical Analysis of Safety Endpoints**

- The frequency and incidence rate of AEs and device malfunctions will be calculated.
- Kaplan-Meier survival analysis may be conducted for time-to-event data.
- Subgroup analysis will be performed based on subject demographics, comorbidities, and treatment history.

**9.4 Reporting of Diseases, Adverse Events, and Device Malfunctions**

1. **Definitions:**
   - Disease events include arrhythmias detected by ILR and other cardiovascular conditions.
   - AEs and device malfunctions will be categorized according to international clinical research guidelines.
2. **Reporting Timeline:**
   - SAE: Immediate reporting within 24 hours.
   - Other AEs: Monthly reports.
3. **Follow-up Actions:**
   - Subjects experiencing AEs will receive appropriate medical treatment and continued monitoring.
   - Device malfunctions will be addressed through technical support and, if necessary, device replacement.

**10. Statistical Analysis**

**10.1 Analysis Sets**

1. **Full Analysis Set (FAS):** Includes all enrolled subjects who received an ILR.
2. **Per Protocol Set (PPS):** Includes subjects who strictly adhered to the study protocol without major deviations.
3. **Safety Analysis Set (SAS):** Includes all subjects implanted with an ILR for safety evaluations.

**10.2 Target Sample Size**

- **Planned Enrollment:** 35 subjects
- **Rationale:**
  - Based on prior studies on ILRs, a sample size of 35 subjects is deemed sufficient to evaluate feasibility and detect major arrhythmic events.
  - Power analysis will be conducted retrospectively.

**10.3 Handling of Cases**

- Subjects who withdraw before ILR implantation will be excluded from analysis.
- Subjects lost to follow-up will be included in the last-observation-carried-forward (LOCF) analysis.

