#### 7.2 Observation/Examination Items and Schedule

##### 7.2.1 Schedule

| **Observation Items** | **Pre-Implant** | **At Implant** | **Remote Monitoring After Implant** |
| --- | --- | --- | --- |
| Informed Consent (IC) | ● |  |  |
| Registration | ● |  |  |
| Subject Background Info | ● |  |  |
| ILR Implantation |  | ● |  |
| Remote Monitoring: arrhythmia events¹ |  |  | 6/12/18/24/30/36 months ±4 weeks |
| 12-lead ECG² | ● | ● |  |
| Echo (LAD, LVDd, LVDs, LVEF, etc.) | ● |  |  |
| Blood test (BNP) | ● |  |  |
| Chest X-ray | ● |  |  |
| Clinical course (every 1–3 months) |  |  | (Ongoing in standard outpatient care) |
| Adverse events, device malfunctions | (Monitored throughout the study) |  |  |

¹ ILR data are evaluated at 6-month intervals (±4 weeks).
² Baseline ECG: can be a monitor ECG at implant.

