**10.5 Statistical Analysis Plan**

1. **Baseline Characteristics:** Descriptive statistics for demographic and clinical characteristics.
2. **Primary Endpoint Analysis:**
   - Incidence of AF and ventricular tachycardia will be analyzed using proportion estimates.
   - Confidence intervals (95% CI) will be reported.
3. **Secondary Endpoint Analysis:**
   - Kaplan-Meier survival curves for time-to-event analyses.
   - Cox regression models for risk factor assessment.
4. **Safety Analysis:**
   - AE incidence and severity will be analyzed descriptively.

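### LOCF with a crude proportion counts patients lost before any detection as arrhythmia-free for time in which they were not monitored, so the primary detection rate is biased downward

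*Protocol*

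**What the plan says.** The primary endpoint (Protocol 5.1 and 8.1.1) is the share of patients with AF, non-sustained VT or sustained VT detected on the implantable loop recorder (ILR). It is an ever-detected endpoint: once positive, a patient stays positive. On timing, section 8.2 says: "The main analysis uses 1-year data; after all have reached 3 years, a final analysis is done".

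For the estimator, section 10.5 says "Incidence of AF and ventricular tachycardia will be analyzed using proportion estimates" and "Confidence intervals (95% CI) will be reported". The same section lists "Kaplan-Meier survival curves for time-to-event analyses", but under the secondary endpoints only.

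For incomplete follow-up, section 10.3 says "Subjects lost to follow-up will be included in the last-observation-carried-forward (LOCF) analysis". It names no endpoint and gives no rule for other ways in which monitoring may stop. The full analysis set in section 10.1 "Includes all enrolled subjects who received an ILR", whatever the monitored time.

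Section 7.1.5 provides for early ends. When an adverse event or device malfunction forces explantation, "the study observation ends at that time". Observation also ends when a new device replaces the ILR or when follow-up is no longer feasible. Section 7.6 repeats these grounds and adds others, such as withdrawal of consent.

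**The concern.** For an ever-detected endpoint, the last observation of a patient with no event so far is a no. LOCF carries that no to the end of the period. A patient lost at month 2 without a detection then scores the same as one monitored for 12 months without an arrhythmia. The plain proportion has no term for monitored time that could correct this.

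The error has one direction. Against the rate under full monitoring, the estimate is equal or too low, never too high, and the confidence interval treats the unmonitored time as observed. It also sits badly with the protocol's own background (section 3), which argues that the yield of ECG monitoring depends on how long the patient is monitored.

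The detection rate is the study's main result, and section 3 says that promising results may lead to a trial to widen the device's indication. The gap grows with loss, so the 3-year final analysis is more exposed than the 1-year analysis.

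The statistical analysis plan is not at hand. The point rests on what the protocol itself fixes, not on detail that it leaves open.

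**Working it through.** **Inputs from the protocol:** 35 subjects (10.2); main analysis at 1 year and final analysis after 3 years (8.2); crude proportion (10.5); LOCF for loss to follow-up (10.3).

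**Inputs not in the protocol:** the detection rate and the loss rate. Section 3 says that the incidence is not known. The values below are assumptions. There is no stated figure to reproduce, because section 10.2 gives no rate, precision or drop-out behind the 35.

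**Model.** Detection has a constant hazard l and loss an independent constant hazard m, both per analysis period.

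- True risk with full monitoring: p = 1 − exp(−l), so l = −ln(1 − p).
- Loss by the end of the period, ignoring detection: q = 1 − exp(−m), so m = −ln(1 − q).
- Expected LOCF/crude proportion: l/(l + m) × [1 − exp(−(l + m))] = l/(l + m) × [1 − (1 − p)(1 − q)].

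**1 year, true 30%** (l = 0.3567)

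- 10% loss (m = 0.1054): 0.3567/0.4621 × (1 − 0.63) = 28.6%, 1.4 points low.
- 20% loss (m = 0.2231): 0.3567/0.5798 × (1 − 0.56) = 27.1%, 2.9 points low.

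One patient in 35 is 2.9 points, so these are about half a patient and one patient. Over a wider assumed range (true 10% to 50%, loss 5% to 30%), the shortfall runs from 0.2 to 7.1 points. For scale, the exact 95% interval for 11/35 is 16.9% to 49.3%.

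**3 years, true 60%** (l = 0.9163)

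- 30% loss (m = 0.3567): 0.9163/1.2730 × (1 − 0.28) = 51.8%, 8.2 points low.
- 40% loss (m = 0.5108): 0.9163/1.4271 × (1 − 0.24) = 48.8%, 11.2 points low.

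**If half of the 3-year stopping hazard is death.** The target is now cumulative incidence with death as a competing event: l/(l + d) × [1 − exp(−(l + d))], with d = m/2. The crude proportion does not change.

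- 30% stopping (d = 0.1783): 0.9163/1.0946 × (1 − 0.3347) = 55.7%, against 51.8%: 3.9 points low.
- 40% stopping (d = 0.2554): 0.9163/1.1717 × (1 − 0.3098) = 54.0%, against 48.8%: 5.2 points low.

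**Check that censoring removes the bias.** In 20,000 simulated trials of 35 patients with independent loss and no deaths, a true 30% at 1 year gave a mean of 30.0% to 30.1% for one minus Kaplan-Meier at 10%, 20% and 30% loss. The crude formula gives 28.6%, 27.1% and 25.5%.

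**One trial by hand.** Suppose 6 detections in the first 6 months, 4 patients lost event-free at 6 months, 3 detections afterwards and no deaths. The crude proportion is 9/35 = 25.7%. With censoring it is 1 − (29/35) × (22/25) = 27.1%.

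**The case against.** The strongest reply is one of scale. The study is exploratory and single-arm, with no hypothesis test or decision threshold, and its main analysis is at 1 year. With up to 20% loss around a true 30%, the bias is one patient or less inside an interval some 32 points wide. The larger 3-year figures rest on loss rates that the protocol does not give. This stands, and it limits the severity. It does not justify LOCF: the direction of the bias is known, the interval does not reflect it, and the alternative is cheap.

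A reader might infer more than the protocol supports:

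- **That every patient who stops early is scored arrhythmia-free.** Anyone with a detection before stopping stays an event. In five simulated 1-year scenarios, 10% to 21% of early stoppers already had one. Among patients explanted for a new device after an arrhythmia, the share may well be higher.
- **That LOCF is prescribed for explantation and device failure.** Section 10.3 names only loss to follow-up. For explantation after an adverse event, malfunction or new device there is no stated rule. The effect is the same only if those patients stay in the full-analysis-set denominator as non-events.
- **That deaths add to the bias.** If death is a competing event, a death without detection is correctly a non-event. With death as the only early stop, the crude proportion and the competing-risk estimate coincide.
- **That the visit window ("6/12/18/24/30/36 months ±4 weeks") distorts the rate.** This would need status to be fixed by the readout date. The protocol does not say so: section 5.1 refers to data at 1 year, and section 7.2.2 records the date and time of AF episodes.
- **That relocation is a large source of loss.** Section 7.1.4 lets subjects who move remain under conditions, and monitoring is remote.

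Nor does this point bear on the Kaplan-Meier analyses of the secondary endpoints.

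**Conclusion.** The concern holds in a limited form. Sections 10.3 and 10.5, followed as written, count each patient lost before any detection as arrhythmia-free for the unmonitored remainder, and this biases the detection proportion downward relative to full monitoring.

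At 1 year the likely size is 1.4 to 2.9 points around a true 30%. By 3 years it may reach 8 to 11 points around a true 60% if all the stopping is non-death loss, or about 4 to 5 points if half of it is death. These figures assume constant, independent hazards and loss rates of 10% to 20% (1 year) and 30% to 40% (3 years). With no loss there is no bias.

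This should be fixed, chiefly for the final analysis. The documents do not support calling the 1-year estimate seriously wrong.

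**What to change.** In Protocol 10.3 and 10.5:

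- Delete LOCF for the detection endpoint.
- Analyse time from implantation to the first adjudicated AF, non-sustained VT or sustained VT episode, placed by its recorded date.
- Censor at the end of valid monitoring: loss, withdrawal, explantation or last valid transmission.
- Treat death before detection as a competing event.
- Report the Aalen-Johansen cumulative incidence with a 95% confidence interval at 1 year (primary) and 3 years (final).
- Keep the crude proportion as a sensitivity analysis.

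In the case report form, record episode dates for non-sustained and sustained VT and the date of the last valid transmission. Section 7.2.2 lists date and time explicitly only for AF.

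The cost is an amendment to the wording, a few data fields and a little programming. The interval becomes slightly wider. Censoring at explantation for a new device may be informative. The crude proportion, which scores all such patients without a detection as non-events, bounds the result from below. If nobody is lost or explanted early, the two estimates are identical.
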